### Monitoring

The time and effort necessary for the self-reported assessments may impose some participant burden. To increase compliance and alleviate participant burden, control group participants will be offered a monetary compensation of 150 NOK (10 NOK ~ 1 EUR) if they report on all questionnaires and ≥ 4 sleep diaries at timepoints T1, T2, T3 and T4, respectively. Moreover, participation in the group-delivered CBT-I is typically subject to a fee (varying from 200–550 NOK between the Healthy Life Centres), but intervention group participants will be exempted from paying this fee.

The study will impose participant focus on insomnia, own sleep, and health-related consequences. For some, this may be perceived as stressful or worrying. However, all participants are seeking out insomnia treatment, and most likely already have an increased focus on these aspects in their daily lives. The harm associated with participation is therefore deemed acceptable. Participants who contact the research team or the Healthy Life centre employees about participation burden will be followed-up individually. All participants will be informed about the possibility to terminate participation in the study for any reason.

Control group participants are placed on a 6-month waiting list before they can participate in the treatment. This waiting time is deemed acceptable, as the usual waiting time for the treatment varies from 1 to 6 months, depending on the centre (i.e., centres in more sparsely populated municipalities have longer waiting periods, as they organize fewer treatment groups). Likewise, some intervention group participants may experience a waiting time of up to 6 months before they can begin treatment. This reflects natural capacity limitations. To alleviate the waiting time, multiple centres will be organizing more frequent treatment groups, and waiting times over 3 months for the intervention group participants will rarely occur. Relevant for all study participants is the notion that participation in the RCT will not be a prerequisite for attending the group-delivered CBT-I treatment at the Healthy Life Centers – those who decline to take part in the RCT will still be able to attend the treatment.

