**Methods:**

A pragmatic multicentre randomized controlled trial will be conducted with about 300 participants recruited across 26 Healthy Life Centres in Norway. Participants will complete online screening and provide consent before enrolment. Those who meet the eligibility criteria will be randomized to a group-delivered CBT-I or to a waiting list according to a 2:1 ratio. The intervention consists of four two-hour sessions. Assessments will be performed at baseline, 4 weeks, 3- and 6 months post-intervention, respectively. The primary outcome is self-reported insomnia severity at 3 months post-intervention. Secondary outcomes include health-related quality of life, fatigue, mental distress, dysfunctional beliefs and attitudes about sleep, sleep reactivity, 7-day sleep diaries, and data obtained from national health registries (sick leave, use of relevant prescribed medications, healthcare utilization). Exploratory analyses will identify factors influencing treatment effectiveness, and we will conduct a mixed-method process evaluation to identify facilitators and barriers of participants’ treatment adherence. The study protocol was approved by the Regional Committee for Medical and Health Research ethics in Mid-Norway (ID 465241).

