#### Control group

Participants in the control group will be placed on a waiting list for 6 months. They will not be restricted from seeking other forms of treatment during the waiting period, nor from using sleep medications. After the waiting period, they will have the possibility to participate in the treatment at their Healthy Life Centre, which will be offered to them by a Healthy Life Centre employee during the waiting period.

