### Assessments

Assessments will be carried out at 6 different time points during the RCT: T1, prior to the intervention; T2, immediately post-intervention; T3, 3 months post-intervention (primary outcome measurement); T4, 6 months post-intervention; T5, 1-year post-intervention; and T6, 2 years post-intervention. The primary outcome is self-reported insomnia severity assessed by the ISI. Several other outcomes will be used in analyses of secondary outcomes, moderators and exploratory mediators, resource use and work productivity, and in a mixed-method process evaluation, described below. Descriptions of all measures, objectives of their use, collected, the participant group receiving them, and the objectives of their use, are provided in Table 2.

**Table 2 Tab2:** Overview of the assessments utilized in the randomized controlled trial

Objective	Measure	Measurement timepoint	Participant group
Demographic information	Self-rated custom questions	T1	All
Primary outcome	Insomnia severity (Insomnia severity index)	Screening, T1, T2, T3, T4	
Secondary outcomes	Health-related quality of life (EuroQol EQ5D-5L)	T1, T2, T3, T4	
	Fatigue (Chalder Fatigue Scale)	T1, T2, T3, T4	
	Mental distress (Hopkins Symptoms Checklist)	T1, T2, T3, T4	
Moderator	Chronotype (Brief Horne-Östberg Morningness-Eveningness Questionnaire)	T1, T2, T3, T4	
Mediators	Unhelpful beliefs about sleep (Dysfunctional Beliefs and Attitudes about Sleep questionnaire-16)	T1, T2, T3, T4	
	Sleep reactivity (Ford Insomnia Response to Stress Test)	T1, T2, T3, T4	
Subjective assessment of sleep patterns	7-day sleep diary	T1, T2, T3, T4	
Mixed-method process evaluation of facilitators and barriers of participants’ treatment adherence in group-delivered CBT-I	Motivation for treatment (Nijmegen Motivation List 2)	T1	~ 60 intervention group participants
	Treatment credibility (Credibility / Expectancy Questionnaire)	T1	
	Adherence to CBT-I components (Treatment Components Adherence Scale)	T3	
	Evaluation of treatment (CBT-I evaluation scale)	T3	
	Individual semi-structured interviews	T2, T3	10–12 intervention group participants
Evaluation of sick leave rates, medication use, and healthcare services utilization	Norwegian Patient Registry	T5, T6	All intervention group participants
	Norwegian Prescription Database	T5, T6	
	National Insurance Administration	T5, T6	

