### Data management and auditing

All self-reported health information will be distributed and collected using the previously described eForsk platform. Upon randomization of each participant, researchers will share an interactive document including participant name, date of birth, phone number and randomization outcome, with the Healthy Life Centre employee to which the participant belongs. In the document, the Healthy Life Centre employee will fill out the date for treatment initiation. Researchers will use this date to plan the distribution of self-report questionnaires. Each Healthy Life Centre will have their own interactive document. Each document will be password protected and shared only with the Healthy Life Centre employees involved in the study.

Upon completion of data collection, an anonymized database will be exported from eForsk, sufficiently encrypted, and stored within the NTNU file system. The participant identification key will be confidential and stored within the eForsk database, with only the project leader having access. All data storage and analysis will be conducted according to the regulations by NTNU and will follow the General Data Protection Regulation. Data will not be disclosed to researchers outside the project or transferred to other countries. A data monitoring committee will not be involved in this study, due to the minimal risks associated with the investigated intervention.

Trial conduct will be audited in line with NTNU’s guidelines. This entails the possibility of an internal quality-assuring control where project information, data management systems, formal approvals, protocol amendments, etc. may be audited. Moreover, two independent project members are employed to follow data collection and management, and to provide support to any participants experiencing issues with the data collection. These project members have regular contact with the Healthy Life Centres participating in the trial. Both the project members and the project leader are informed about withdrawals from the study, and possible adverse events are reported to the Healthy Life Centre employees by the participants.

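### Follow-up is timed from treatment while controls are released after 6 months: intervention-arm T4 always falls past month 6 from randomisation, T3 only after a wait of about 2 months, and the text does not date the control visits

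*Protocol article*

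**What the plan says.** Randomisation follows consent, and only then does the centre contact intervention participants about its next group (Eligibility and procedure). The wait before treatment therefore lies after randomisation. On its length, Monitoring says that "the usual waiting time for the treatment varies from 1 to 6 months, depending on the centre", that "some intervention group participants may experience a waiting time of up to 6 months before they can begin treatment", and, because extra groups are being organised, that "waiting times over 3 months for the intervention group participants will rarely occur".

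Follow-up is defined relative to treatment: "T3, 3 months post-intervention (primary outcome measurement); T4, 6 months post-intervention" (Assessments). The centre enters each treatment start date in a shared document, and "Researchers will use this date to plan the distribution of self-report questionnaires" (Data management and auditing).

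For the other arm, "Participants in the control group will be placed on a waiting list for 6 months", and "After the waiting period, they will have the possibility to participate in the treatment at their Healthy Life Centre" (Control group). The same section says the offer is made while they are still waiting. Controls are invited to the same four assessments (Eligibility and procedure) and are paid for completing T1 to T4 (Monitoring).

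The primary analysis compares the T1 to T3 change in ISI between arms (Statistical analysis plan). Secondary aim (i) concerns effectiveness on other outcomes at 3 and 6 months after treatment (Aims).

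**The concern.** The intervention arm's visits follow the treatment date, which moves with the centre's capacity. The control arm's untreated period has a fixed length. A control has no treatment date during the wait, and the text gives no substitute anchor for T1 to T4 in that arm.

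Two things are at stake. If control visits are matched in time to intervention visits, T4 comes after controls may have started the same therapy, and the 6-month comparison is no longer CBT-I against a waiting list. If control visits run from randomisation instead, the arms are observed at different times since randomisation. Entry requires an ISI of at least 12, so some regression to the mean is expected. Natural remission, regression to the mean and season could then act over different periods in the two arms of the primary contrast.

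**Working it through.** **Inputs**
- w, months from randomisation to treatment start: up to 6, rarely over 3 (Monitoring). Its distribution is not given.
- d, course length: "The intervention consists of four two-hour sessions" (abstract, Methods), with spacing not stated. Assumption: 3, 4 or 6 weeks. With 12/52 month per week, d = 0.69, 0.92 or 1.38 months.
- Control wait: 6 months, start not stated. Assumption: randomisation.

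The plan gives no figure of its own to reproduce here.

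**Intervention-arm visits, in months from randomisation**

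T3 = w + d + 3 and T4 = w + d + 6.

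| w | T3 (d = 3 to 6 weeks) | T4 (d = 3 to 6 weeks) |
|---|---|---|
| 0 | 3.7 to 4.4 | 6.7 to 7.4 |
| 1 | 4.7 to 5.4 | 7.7 to 8.4 |
| 2 | 5.7 to 6.4 | 8.7 to 9.4 |
| 3 | 6.7 to 7.4 | 9.7 to 10.4 |
| 6 | 9.7 to 10.4 | 12.7 to 13.4 |

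T4 exceeds 6 for every w, because d > 0. T3 exceeds 6 only if w > 3 − d, which is 2.31, 2.08 or 1.62 months for d = 3, 4 or 6 weeks.

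**How many T3 visits that is.** The document does not allow a count. As illustration only, waits spread evenly over 0 to 3 months would put (3 − 2.31)/3 = 23% to (3 − 1.62)/3 = 46% of T3 visits past month 6. Spread evenly over 1 to 3 months, the share would be (3 − 2.31)/2 = 35% to (3 − 1.62)/2 = 69%.

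**Three ways to date control visits**
1. *Mirroring the intervention arm, from randomisation.* Control T4 falls at w + d + 6, after release. A control who starts at month 6 finishes at 6 + d = 6.7 to 7.4. With w = 0 the mirrored T4 meets that control at the end of the course at the earliest. With w = 3 it comes 3 months after the course.
2. *From randomisation, without the course length.* Control T3 is at month 3 and T4 at month 6, the edge of the wait. The arms then differ in time since randomisation by w + d: 0.7 to 1.4 months with no wait, and 3.7 to 4.4 with a 3-month wait.
3. *From a T1 placed just before treatment, and moved equally in controls.* The T1 to T3 interval is d + 3 = 3.7 to 4.4 months in both arms whatever the wait, so the primary contrast is aligned. T4 is d + 6 months after T1. Even if the 6-month wait were counted from T1, T4 would fall 0.7 to 1.4 months after it ends.

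**What treated controls could do to the T4 contrast (hypothetical).** The Sample size section implies an SD of (6.2 − 1.4)/0.86 = 5.58 ISI points, so the planned effect of 0.50 is 0.50 × 5.58 = 2.79 points. If a share c of controls had gained that full benefit by T4, the expected contrast would be 2.79 × (1 − c): 2.1, 1.4 and 0.7 points for c = 25%, 50% and 75%. The document gives no basis for choosing c.

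**The case against.** The other side has substance on several points.

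- **T3 is often late.** A reader who takes only the 6-month maximum might infer this. The same paragraph says that waits over 3 months will be rare, and no distribution is given. T3 is late for waits above roughly 2 months; that this is frequent is not shown.
- **The sections contradict each other.** A reader might infer this too, but they can coexist. Uptake by controls is optional and depends on the next group, so passing month 6 permits crossover without showing it.
- **The primary contrast is biased.** This does not follow. T1 is only said to precede the intervention. If it is tied to the treatment date and moved equally in controls, the T1 to T3 intervals match.
- **The control schedule may be elsewhere.** Fig. 1 and the SPIRIT chart in the supplement are not shown and may contain a rule. This limits confidence.
- **Remedies have limits.** A shared index date aligns the arms but leaves T4 past month 6. Groups form as participants accrue, so a group date may not exist at randomisation. Dropping control data after crossover from the primary analysis would depart from intention to treat.

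These points narrow the concern without removing it. Each reading of the visible text leaves either arms measured at different times since randomisation or control T4 data taken after access to the same therapy. The Discussion lists dropout and other treatments during the wait as limitations, but not this. It is also a matter of design: an analysis plan cannot recover untreated T4 data once controls have been treated.

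**Conclusion.** The concern holds in a limited form. Intervention-arm T4 falls after month 6 from randomisation for every participant: 6.7 to 7.4 months with no wait and 9.7 to 10.4 with a 3-month wait. T3 does so only when the wait exceeds about 1.6 to 2.3 months, in an unknown share of participants. These figures assume a 3- to 6-week course and a control wait that starts at randomisation.

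The 6-month contrast is therefore not secured as a comparison with an untreated waiting list. The primary contrast is exposed to unequal timing unless control visits, T1 included, are dated in the same way as intervention visits. Neither bias is demonstrated, and the dilution figures are conditional on an unknown crossover share. The point should be corrected, but it is not a fatal flaw. Confidence is medium, because the control schedule may stand in material not shown.

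**What to change.** 1. State one index date that sets T1 to T4 in both arms, for example a centre-level date assigned in the same way regardless of allocation.
2. Record days from randomisation to each assessment, and the date on which any control starts group CBT-I. Add a sensitivity model for ISI that uses actual timing.
3. Reconcile the Control group, Assessments, Data management and auditing, and Monitoring sections on waiting period and assessment timing. How to do so is the sponsor's decision.
4. Keep the intention-to-treat analysis as primary. Add a sensitivity analysis that does not treat control ISI recorded after the start of group CBT-I as untreated data.
5. If T4 cannot lie inside the waiting period, report it as early versus delayed access to CBT-I and not as CBT-I versus waiting list.

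The cost is a change to questionnaire send-dates in eForsk, a few recorded dates, protocol wording and two sensitivity analyses. No extra participants are needed. Recruitment began in August 2022, so for assessments already completed only the recording and analysis steps can apply. The price is a weaker claim at T4.

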### Patient and public involvement

Multiple representatives of the Healthy Life Centers, and a representative of a mental health user group, were involved during study conceptualization, design, and conduct. During study design, 5 earlier treatment participants were asked to test and evaluate the self-reported assessments. To user groups, and public and patient stake holders, findings will be disseminated using user-friendly outputs.

## Discussion

This nation-wide, pragmatic RCT with 26 participating centres will investigate the effectiveness of group-delivered cognitive behavioural therapy versus waiting list in the treatment of insomnia. Primary outcome is insomnia severity at 3 months post-treatment. While this trial will generate novel findings about insomnia treatment in interdisciplinary primary care services, there are also a number of limitations. First, as the recruitment strategy is based on voluntary participation and self-referral, there is a possibility of participant self-selection bias. Second, even though all Healthy Life centres employees participating in the trial had prior experience with delivering the intervention, and all attended an information meeting about the research project to ensure a common knowledge basis for all instructors, there is a lack of treatment integrity investigation at the 26 participating centres. Thus, it is possible that there may be quality differences in treatment administration between the participating centres. Third, no objective measurements of sleep are employed in the trial. Fourth, since data at the first four measurement timepoints is based on self-report, there is a possibility of missing data and sample attrition. Participants who do not adhere to the data collection will be followed up to mitigate some of the associated risk. Lastly, the 6-month waiting period for the control group may lead to dropout from the trial or use of other treatment options during the intervention.

## Data Availability

Not applicable.

## Abbreviations

CBT-I: Cognitive behavioural therapy for insomnia
RCT: Randomized controlled trial
SPIRIT: Standard Protocol Items for Randomized Trials
NTNU: Norwegian University of Science and Technology
ISI: Insomnia Severity Index
